## Method/design

### Trial design

This study is a randomized controlled trial (RCT) comparing the effects of CKC versus OKC versus the control group in patients with mild knee OA. The effects to be measured include pain, disability, quality of life, and lower limb biomechanics. This protocol will be outlined as per the CONsolidated Standards of Reporting Trials (CONSORT) [19] statement and reported as per Standard Protocol Items: Recommendations for Interventional Trials (SPIRIT) [20]. The flowchart of the study protocol is shown in Fig. 1.

**Fig. 1 Fig1:**
[figure not shown]
Participant flow through the randomized controlled trial

All participants will be assigned randomly to one of the three groups (CKC, OKC, or control groups) by an independent researcher. The allocation numbers will be generated by the study supervisor using a computerized random sequence. The 66 numbers will be inserted in opaque and sealed envelopes until a participant picks an envelope. The participants will then be allocated to the group stated in the envelope. A sealed copy of the randomization code listing will be kept by the study supervisor, and it will not be revealed until the study completion. Additionally, two research team members are designated as outcome assessors for the pre-and post-intervention tests. They will also be blinded to the group allocation and the statistical analyses. Participants will be reminded not to reveal their group allocation to the assessors. The study procedure will follow the Declaration of the Helsinki as approved by the Human Research Ethics Committee at the Universiti Sains Malaysia (JEPeM code: USM/JEPeM/19100645). The protocol has been registered at clinicaltrial.gov (NCT04678609).

The printed information sheet that explains this study will be given to the potential participants together with the consent form. These forms will be produced in a bilingual format in both Malay and English to ensure that all participants understand the research procedure. Participants will give their consent to start the pre-test and intervention sessions by signing the form. The form will also be signed by a witness and the researcher.

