### Monitoring

The researcher will be responsible for monitoring all the subject enrollment, the reasons for dropping out, and the listing of all the adverse events to prepare all the relevant reports. The researcher will also arrange a follow-up appointment with the medical officer for any drop-out participants. Regular meetings will be held every 2 weeks between the study supervisor and researchers to monitor any adverse events from the exercise program and to ensure timely completion of participants’ recruitment. Close communication will be maintained between the assessors and researchers to monitor any problems that arise during the stages of data collection and intervention implementation. Lastly, the study supervisor will conduct monthly audits of the raw data collected, as well as the interventions in the clinical trial. Any protocol modifications that are required during the study period will be submitted to the Ethics Committee of the Universiti Sains Malaysia for approval before further implementation.

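### Close contact between assessors and researchers puts assessor blinding at risk, and letting participants pick an envelope leaves the allocation order unenforced

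*Protocol article*

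**What the plan says.** **Assessors.** The Trial design section (text after Fig. 1) names two team members as assessors for the tests before and after the intervention, and states: "They will also be blinded to the group allocation and the statistical analyses". The Procedure section repeats that they do not know the arm. The stated safeguard is a reminder to participants to keep their group to themselves. The Monitoring section then says: "Close communication will be maintained between the assessors and researchers to monitor any problems that arise". The rest of that sentence names two stages in which such problems may arise: collecting the data and implementing the intervention.

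**Allocation.** The same Trial design text says that participants are "assigned randomly to one of the three groups (CKC, OKC, or control groups) by an independent researcher". It continues: "The allocation numbers will be generated by the study supervisor using a computerized random sequence". Then: "The 66 numbers will be inserted in opaque and sealed envelopes until a participant picks an envelope", followed by: "The participants will then be allocated to the group stated in the envelope". On the list itself: "A sealed copy of the randomization code listing will be kept by the study supervisor, and it will not be revealed until the study completion".

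**The concern.** Two stated procedures pull against the protections that the article claims.

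First, staff who must not know the arm are told to stay in close touch with staff who do, on a subject that can disclose it. If an assessor learns the arm, encouragement, repeat trials and handling during maximal-effort or laboratory tests may differ between arms without anyone intending it.

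Second, a computer-generated sequence protects against selection only if it is followed. Where the participant's choice of envelope decides the arm, no order exists to depart from. Someone who lets a participant pick again, or who sets an opened envelope aside for a later participant, breaks no visible rule. At stake is the assurance that the groups differ only by chance.

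**Working it through.** The article gives no figure on this point, so the check sets its statements side by side.

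**Step 1: can intervention problems reveal the arm?**
- OKC: straight leg raises, seated knee extension, and hip abduction and adduction lying down.
- CKC: terminal knee extension in standing, wall slides, and forward and side step-ups.
- Control: printed education and no exercise information.

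A complaint about the step, the wall slide or leg raises in bed points to one arm. An ordinary description of a problem would therefore often identify the group.

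**Step 2: is the exchange restricted?** The instruction to participants to stay silent has no counterpart for researchers. The Monitoring sentence includes intervention implementation and does not exclude information that reveals allocation. A channel that avoids the assessors already exists: under Adverse event, participants report problems to the physiotherapist, who contacts the medical supervisor and co-supervisors if needed.

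**Step 3: which outcomes depend on assessor blinding?**

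| Outcome | Status | Who produces the value | Exposed if the assessor learns the arm |
|---|---|---|---|
| VAS, WOMAC, OAKHQOL | primary | the participant, who knows her arm | little |
| Isokinetic strength | secondary | maximal effort under an assessor | yes |
| Gait and sit-to-stand biomechanics | secondary | laboratory test run by an assessor | yes |

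That participants know their arm follows from the reminder not to disclose it.

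**Step 4: what fixes the allocation?** The supervisor generates a sequence, 66 numbers go into envelopes (3 × 22 = 66, matching the sample size section), a participant picks one, and its content decides the group. The generated order therefore has no effect on who gets which arm. Each pick is still a random draw from opaque, sealed envelopes, so its content is hidden beforehand. What is lost is a predetermined next envelope. With one, a skipped or swapped envelope shows as a break in order. With a free pick, two participants' envelopes could be exchanged and the final counts would still be 22 per group.

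**Step 5: can the size be derived?** No. The documents give neither a rate of re-picks nor a rate or effect of assessor unblinding.

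**The case against.** The case on the other side is substantial, and much of it stands.

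- *Concealment.* A reader might infer that the procedures undo it. They do not. Opaque sealed envelopes hide the arm, and under a free pick even the holder of the list cannot foretell the next assignment. Assignment by an independent researcher is also compatible with that researcher presenting the envelopes.
- *Audit.* A reader might infer that allocation cannot be audited. The article does not show this: a picked number may be traceable to the retained listing. Nor is silence about a log a fault, since an article commonly leaves that to the full protocol. The point rests only on the pick that the article does describe.
- *The supervisor.* The same person generates and keeps the list, and "the study supervisor will conduct monthly audits of the raw data collected, as well as the interventions in the clinical trial". A reader might take that as a breach. The audits follow assignment, and the article does not say that the supervisor enrols participants, tests outcomes or is blinded. No objection is made here.
- *Predictability.* Assuming 22 envelopes per arm, a person who knew every past allocation could guess the next arm about 42% of the time on average (5,000 simulated draws), against 33% without that knowledge. This comes from the fixed 22/22/22 total. Numbered envelopes from the same total give the same figure, so it does not measure a defect of picking, and the fix would not change it.
- *Blinding.* The Monitoring sentence does not say that allocation is disclosed, and the physiotherapist channel already handles participants' problems. That is fair: the sentence opens a route to unblinding and does not prove it. But the sentence includes intervention problems in the assessors' contact, and the blinding statement cannot be relied on until the two are reconciled.

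**Conclusion.** The concern holds in a limited form.

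1. **Assessor blinding is put at risk** by the Monitoring section's own wording. This is the stronger part. It concerns mainly isokinetic strength, gait and sit-to-stand, and hardly the self-reported primary outcomes. It assumes that the researchers in contact with assessors know the arms, which is likely for anyone dealing with intervention problems but is not stated.
2. **The allocation order is not enforced**, because the participant's pick replaces the generated sequence. A re-pick, swap or discarded envelope could go undetected under the procedure as described. Nothing in the documents suggests that this has happened.

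Neither bias can be sized from the documents. Both changes are worth making because they remove avoidable risks almost for free; neither fault by itself invalidates the trial.

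**What to change.** **Communication.** Amend the Monitoring section so that contact between assessors and researchers covers data-collection matters only. Route intervention problems through the physiotherapist channel already described under Adverse event, and state that nothing revealing allocation may reach the assessors. This also helps participants already randomized who still await their post-intervention tests.

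**Allocation.** For envelopes not yet used, the independent researcher shuffles them unopened, numbers them in sequence, and opens the next in order only after consent and baseline assessment, logging participant ID and date. Counting them first is a useful check: the number left should be 66 minus the number already allocated. The list should not be regenerated, and unmarked envelopes should not be sorted back into the original computer order, which would mean opening them. Shuffling and numbering gives a random order fixed in advance without that.

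**Reach and cost.** Under Trial status, recruitment was still open and expected to end on 30 June 2022, so the envelope change reaches only participants not yet allocated; the report should describe how earlier ones were assigned. The cost is a short amendment for the ethics committee, relabelling, a log and one communication rule. Staff, outcomes and sample size do not change.

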### Sample size calculation

The sample size was determined using G*Power statistical software version 3.1.9.2 (Universität Düsseldorf, Germany) based on the primary outcome variables of pain and function based on the visual analog scale (VAS) scores as well as the Western Ontario and McMaster Universities Arthritis (WOMAC) Index respectively. The sample size for this study was determined to detect an effect size of 0.5, based on a previous study [21] with an alpha value of 0.05. Eighteen participants per group will be sufficient to achieve a statistical power of 0.8. By anticipating a dropout rate of 20%, a total of 22 participants per group (total *N* = 66) will be recruited.

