To date, open kinetic chain (OKC) and closed kinetic chain (CKC) exercises have been prescribed for knee OA patients. During OKC exercise, the distal segment of the body parts is not fixed, and it can move freely. Knee extension in the sitting position and straight leg raising (SLR) in the lying position are examples of OKC exercises. On the other hand, during CKC exercise, the distal segment of body parts remains stationary on the ground. Examples of CKC exercises include squat and leg press exercises. Both types of exercises were comparable in terms of their impact on improving pain scale, functional scores, and strength [16]. Moreover, 12 weeks of OKC, CKC, and its combination were found to significantly increase the static and dynamic quadriceps strength and thigh muscle bulk in a study that involved 96 patients with knee OA [17]. However, there is a lack of published studies that evaluate the impact of OKC and CKC on the lower limb biomechanics during gait and STS.

Exercise intervention for OA is usually conducted in the hospital or clinic under the supervision of physiotherapists. However, some patients might face logistics constraints in attending the exercise sessions [18]. To improve the adherence to exercise program, the sessions can be relocated from the hospital to other settings such as at home and in the community [7]. Apart from that, patient education is vital to improve the patients’ understanding of their current condition and to ensure compliance to exercise program and long-term self-management at home [12].

The primary aim of this randomized controlled trial (RCT) is to compare the effects of home-based OKC and CKC exercise intervention programs on pain (visual analog scale), disability scores (Western Ontario and McMaster Universities Arthritis Index), and quality of life scores (Osteoarthritis Knee and Hip Quality of Life) among patients with mild knee OA. Our secondary aim is to compare the effects of OKC and CKC exercises on lower limb biomechanics during walking gait and STS tasks. It is hypothesized that OKC and CKC exercises will result in a significant reduction of pain as well as improved functions and quality of life after 8 weeks of intervention. We also hypothesize a small but clinically relevant change in their biomechanical variables following OKC and CKC intervention. These changes may be significant when compared to the usual care group.

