## Discussion

The prevention of knee OA is different for each individual depending on their risk factors [46]. Targeted individualized prevention techniques to ensure maximum adherence to the exercise program should be planned for each patient [46]. To achieve this, it is crucial to involved knee OA patients in the exercise program to understand their treatment preferences and improve their conditions. Apart from statistically significant differences between patient and control groups, other clinically significant differences can also be important when interpreting the trial results [47, 48]. A decrease of 2 points in the pain score and a decrease of 9.1 scores in the function subscale of the WOMAC questionnaire are examples of clinically relevant improvement [47, 49, 50]. A mere 5% change in KAM was shown to improve OA symptoms [51, 52] which will be considered as a clinically relevant improvement of the KAM in this trial. The results from this trial will provide vital evidence on clinical and biomechanical outcomes following OKC and CKC exercise programs in people with mild knee OA. Additionally, this study will help in the formulation of effective home-based exercise protocols, especially for patients with mild knee OA.

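### The sample size paragraph does not fix what an effect size of 0.5 means, 18 per group does not reproduce under the usual readings, and power for OKC versus CKC at 0.5 SD is about 31%, not 80%

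*Protocol article*

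**What the plan says.** The section Sample size calculation says that the sample size "was determined to detect an effect size of 0.5", taken from a previous study, "with an alpha value of 0.05", using G*Power and based on VAS pain and WOMAC function. It concludes that "Eighteen participants per group will be sufficient to achieve a statistical power of 0.8". It then adds: "By anticipating a dropout rate of 20%, a total of 22 participants per group (total *N* = 66) will be recruited". It does not give the effect-size metric, the test, the number of groups entered, the sidedness or a pre-post correlation.

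The Background says that the primary aim "is to compare the effects of home-based OKC and CKC exercise intervention programs on pain", and on disability and quality of life. It also says of earlier evidence on OKC and CKC: "Both types of exercises were comparable in terms of their impact on improving pain scale, functional scores, and strength". The section Statistical analysis plans a two-way ANOVA followed, where significant, by LSD pairwise tests. The Discussion gives "A decrease of 2 points in the pain score" as an example of a clinically relevant improvement.

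**The concern.** Effect size, alpha, power and n per group are all printed, so they should fit together under some ordinary test. The answer depends heavily on what 0.5 means: as d it is half a standard deviation between two arms, while as f it describes the spread of three means and implies much larger gaps. A reader cannot tell which contrast the 80% belongs to.

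The primary aim is a comparison of two active exercise programmes that the protocol itself describes as comparable on earlier evidence. A small OKC-CKC difference is therefore a realistic case. If 80% power is taken to cover that contrast when it does not, a non-significant result carries much less information than the reader has been led to expect.

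**Working it through.** **Inputs from the protocol.** Effect size 0.5; alpha 0.05; power 0.8; 18 evaluable per group (54 in total); three equal groups; pre and post measurement. **Assumed.** Two-sided tests; pre-post correlation r, which the protocol does not give.

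**Step 1: try to reproduce 18 per group.** Powers come from the noncentral t or F distribution, with n per group and N in total.

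- *Two-sample t, d = 0.5.* Noncentrality d√(n/2). At n = 18 it is 0.5 × √9 = 1.5 with 34 df, power 0.31. Power 0.80 needs n = 64 (one-sided: 51).
- *Paired t, d = 0.5.* Noncentrality d√n. Power 0.80 needs n = 34; at 18 power is 0.52.
- *One-way ANOVA, three groups, f = 0.5.* Noncentrality f²N. Power 0.80 needs N = 42 (0.25 × 42 = 10.5), so 14 per group. At N = 54 (0.25 × 54 = 13.5) power is 0.90.
- *Group-by-time interaction, f = 0.5, two occasions, r = 0.5.* Noncentrality f²N·2/(1 − r). N = 15 suffices (0.25 × 15 × 2/0.5 = 15), so 5 per group; with r from 0 to 0.8, 3 to 8 per group.
- *Nearest miss: two groups, f = 0.5 (d = 1.0).* 17 per group, power 0.83 at 18; three such arms total 51, not 54.

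**Step 2: what does match.** Each match needs an input that the protocol does not state.

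- Interaction with f = 0.25 (not 0.5) and r about 0.34: noncentrality 0.0625 × 54 × 2/0.66 = 10.2, power 0.80 at N = 54.
- A 3 × 3 fixed-effects factorial, f = 0.5, 4 df for the interaction: power 0.81 at N = 54. This assumes three occasions and ignores within-person correlation, so its 54 are independent observations, not participants.

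**Step 3: power for the primary aim at 0.5 SD, 18 per arm.**

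| Analysis | Standardised difference | Power |
|---|---|---|
| Post score, two-sample t | 0.5 | 0.31 |
| Pairwise with pooled three-group error (51 df) | 0.5 | 0.31 |
| Change score, r = 0.5 | 0.5/√(2 × 0.5) = 0.5 | 0.31 |
| Baseline-adjusted, r = 0.5 | 0.5/√(1 − 0.25) = 0.577 | 0.39 |
| Baseline-adjusted, r = 0.7 | 0.5/√(1 − 0.49) = 0.700 | 0.53 |
| Baseline-adjusted, r = 0.8 | 0.5/√(1 − 0.64) = 0.833 | 0.68 |

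With all 22 per group evaluable, the unadjusted figure is 0.37.

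**Step 4: detectable pairwise difference at 80% power, 18 per arm.** Unadjusted: 0.96 SD. Baseline-adjusted: 0.96 × √(1 − r²), which is 0.83 SD at r = 0.5 and 0.69 SD at r = 0.7.

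**Step 5: what f = 0.5 implies.** f is the standard deviation of the group means over the common SD.

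- Two equal exercise arms against control, means (0, g, g): f = g√2/3, so g = 0.5 × 3/√2 = 1.06 SD, and the OKC-CKC gap is zero.
- Evenly spaced means (0, g/2, g): f = g/√6, so g = 0.5 × √6 = 1.22 SD from lowest to highest.

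In the first pattern the overall test has its full power, and none of it concerns OKC versus CKC.

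**The case against.** The strongest reply is that 0.5 was never described as a pairwise d. If it is f in a three-group ANOVA, 18 per group is more than enough for the overall test, and the sentence about sufficiency is true. That stands. A three-arm design also fits an overall effect size: the hypotheses include improvement under both exercises, and comparison with usual care is mentioned. For exercise versus control at 1.06 SD, 18 per arm has power 0.87. The 3 × 3 factorial in Step 2 also shows that 54 can be reached with f = 0.5, although only against the pre-post design described and with repeated measures treated as independent.

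The source of the 0.5 cannot be seen, and a fuller protocol may name the G*Power test. Nor is the detectable difference absurd: if the VAS SD were 2 cm (an assumption; range 1.5 to 2.5), 0.96 SD would be 0.96 × 2 = 1.9 cm (1.4 to 2.4), near the 2 points in the Discussion.

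Three stronger readings are tempting but unsupported. A reader might infer that the trial should have had 64 per group; that follows only if 0.5 is a pairwise d, which the protocol does not say. A reader might infer that the calculation is too optimistic throughout; under f it is conservative for the overall test. A reader might infer that the authors intend to claim equivalence from a non-significant result; no section says so.

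What the reply leaves untouched is that the metric and test are not fixed, and that no reading gives 80% power for OKC versus CKC at 0.5 SD.

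**Conclusion.** The point holds as one of underspecification with a definite consequence for the primary aim. The printed combination of 0.5, 0.8 and 18 does not reproduce under the usual readings, which give from about 5 to 64 per group, and a match needs inputs that are not stated. Whatever 0.5 means, a 0.5 SD difference between OKC and CKC has power 0.31 with 18 evaluable per arm, rising to 0.39, 0.53 or 0.68 with baseline adjustment at r = 0.5, 0.7 or 0.8. Power of 80% is reached at about 0.96 SD unadjusted.

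The pairwise figures assume two-sided alpha 0.05, equal arms of 18, common variance and no multiplicity adjustment. The correlations are assumed values. The choice of 0.5 SD as the OKC-CKC target is a benchmark set by this check, not one that the protocol states.

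**What to change.** Rewrite the sample size paragraph with N unchanged:

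- State whether 0.5 is d or f, and name the test, the groups and occasions entered, and any correlation assumed.
- State that 18 per arm detects a pairwise difference of about 0.96 SD with 80% power, and that power for 0.5 SD between OKC and CKC is about 31% unadjusted.
- If a baseline-adjusted comparison is adopted, give about 0.83 SD at r = 0.5 and 0.69 SD at r = 0.7 instead, with the correlations marked as assumptions. This would change the two-way ANOVA with LSD tests in the section Statistical analysis, so it should be presented as a change of analysis and not as a rewording.
- Commit to reporting OKC minus CKC with its 95% confidence interval, and to not interpreting a non-significant difference as equivalence.

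No extra participants are needed. The cost is that the stated power becomes less favourable and, if baseline adjustment is adopted, an amendment to the planned analysis.

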### Recruitment of participants

This study will apply purposive sampling for the recruitment of participants. Participants will be included if they:
Are diagnosed with symptomatic knee OA as defined by the American College of Rheumatology’s Clinical Criteria for Classification and Reporting of knee OA [22–24]Are diagnosed with Grade I and II knee OA based on the Kellgren-Lawrence severity scale [25]Are femaleAge 50 and olderHave body mass index (BMI) between 18.5 and 29.9 kg/m^2^Have knee pain ≥ two on a VAS

Participants with the following conditions will be excluded:
Electrical devices implantNeurological disorders (i.e., stroke)Wheelchair boundSignificant cognitive impairmentPresent systemic inflammatory arthritis (i.e., gout)History of hip or knee arthroplastyHistory of trauma or surgical arthroscopy of either knee in the last 6 monthsReceived knee intra-articular injection within the last 3 monthsUnder anticoagulant therapy, recent or imminent surgery (within 3 months)Involved in any study related to exercise program within the last 6 months

In addition, eligible participants will be considered as drop-outs if they request to withdraw due to any reasons or if they are unable to complete 75% of the intervention program.

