### Statistical analysis

Data will be entered and analyzed using SPSS version 25 (IBM Corp., Armonk, NY, USA). Only the data from the participants who have completed at least 75% of the study intervention will be analyzed. Data from drop outs will not be included in the analysis. Descriptive data will be reported as a mean ± standard deviation. Two-way ANOVA will be used to test the within- and across- group comparison of the VAS, WOMAC, and OAKHQOL scores, and isokinetic knee muscle strength, as well as lower limb biomechanics during gait and STS. The level of significance is set at a *p*-value < 0.05. A least significant difference (LSD) post hoc test will be conducted following any significant differences from the two-way ANOVA test.

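### The allowance for 20% drop-out is slightly short: 22 per group leaves an expected 17.6, not the 18 that the protocol calls sufficient

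*Protocol article*

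**What the plan says.** The protocol article, under Sample size calculation, gives three linked figures.

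- The evaluable target: "Eighteen participants per group will be sufficient to achieve a statistical power of 0.8".
- The design inputs: the study is sized "to detect an effect size of 0.5, based on a previous study [21] with an alpha value of 0.05". The article does not say whether 0.5 is a standardised difference between two groups (d) or an ANOVA effect size (f).
- The recruitment figure: "By anticipating a dropout rate of 20%, a total of 22 participants per group", for a total of 66. The Trial design section uses the same total for the allocation envelopes. No inflation formula is given.

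Two other sections fix what a drop-out means for the analysis. Under Recruitment of participants, a drop-out is anyone who withdraws for any reason, and also anyone who qualifies "if they are unable to complete 75% of the intervention program". Under Statistical analysis, "Data from drop outs will not be included in the analysis".

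**The concern.** An inflation for drop-out exists to protect the evaluable number. Here the recruited number, reduced by the stated drop-out rate, does not return the stated evaluable number. A reader who takes the section at face value will believe that 18 per group are still expected after a 20% loss. They are not.

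The slip reaches the analysed sample directly. The article describes no analysis of all randomised participants that would absorb the loss, and its definition of drop-out is wide because it includes low adherence as well as withdrawal. What is at stake is whether the sample size statement is correct as written, together with a small amount of nominal power. The validity of the trial is not at stake.

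**Working it through.** **Inputs, all from the protocol article**

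- Evaluable target: 18 per group, three groups, 54 in total (Sample size calculation)
- Drop-out: 20% (same section)
- Recruited: 22 per group, 66 in total (same section)
- Drop-outs excluded from the analysis (Recruitment of participants; Statistical analysis)

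**1. Reproducing the stated 22.** Multiplying by one plus the drop-out rate gives 18 × 1.20 = 21.6, which rounds up to 22. Dividing by the retained fraction gives 18/(1 − 0.20) = 22.5, which gives 22 only if rounded down. Either route could have produced the figure.

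**2. What 22 delivers.** Expected evaluable = 22 × (1 − 0.20) = 17.6 per group, or 66 × 0.80 = 52.8 in total. Against 18 and 54, the shortfall is 0.4 per group and 1.2 in total.

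**3. What a 20% allowance requires.** 18/(1 − 0.20) = 22.5, rounded up to 23 per group, or 3 × 23 = 69. Rounding once on the total gives 54/0.80 = 67.5, so 68. Check: 23 × 0.80 = 18.4, which is at least 18.

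**4. What 22 actually allows for.** 22 − 18 = 4 losses per group, and 4/22 = 18.2%.

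**5. Effect on power, conditional on 18 giving exactly 80%.** Take a one-way ANOVA with three groups, alpha 0.05 and noncentrality N × f². Solving for 80% power at N = 54 gives f = 0.435. This value is back-calculated and does not appear in the article. With f held there:

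| Evaluable per group | Power, three-group ANOVA | Power, two-group t test set to 80% at 18 |
|---|---|---|
| 18 | 80.0% | 80.0% |
| 17.6 | 79.0% | 79.1% |
| 17 | 77.4% | 77.6% |

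**6. Does that condition hold?** It cannot be checked, because the metric of the 0.5 is not given.

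- If 0.5 is f in a three-group one-way ANOVA, 14 per group already gives 80.3%. Eighteen gives 90.2% and 17.6 gives 89.4%, so power does not fall below 80%.
- If 0.5 is d between two groups, 64 per group are needed by the t test and 18 gives about 31%, so 22 against 23 makes no practical difference.
- Repeated-measures versions with f of 0.25 or 0.5 and a correlation from 0 to 0.75 did not give 18 as the required number in any case tried.

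**7. Chance of keeping 18.** If each participant is lost independently with probability 20%, a group of 22 keeps at least 18 with probability 0.543, and all three groups do so with probability 0.543³ = 0.160. With 23 per group the figures are 0.695 and 0.695³ = 0.335. Even a correct inflation would therefore miss 18 in at least one group about two times in three. The low probability at 22 is mostly ordinary binomial variation and should not be charged to the slip.

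**The case against.** The strongest reply is that this is a matter of rounding. The exact inflated number is 22.5, so 22 is half a participant short per group. On the total, 66 is two below 68, and only rounding up in each group separates it by three, from 69. A 20% drop-out rate is itself a guess, and a rate of 18.2% would make the plan exact. One point of power is well inside that uncertainty, and no decision on design or analysis turns on it. All of this stands, and it is why the point is minor. It does not make the sentence correct, since at the stated rate the stated number falls below the stated target.

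The second reply is that the article calls 18 sufficient and does not call it the minimum. This also stands. A reader might infer that the trial has less than 80% power because of the inflation step. The article does not support that: it depends on 18 giving exactly 80%, and under one plausible reading of the effect size (f = 0.5) power stays near 89% at 17.6 per group.

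The third is that the cause is unknown. A reader might infer that the drop-out rate was multiplied on instead of divided out. The figure fits that, but it also fits 22.5 rounded down, and the article shows no formula. The cause should be left open.

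**Conclusion.** The point holds as a small internal inconsistency: at 20% loss, 22 per group does not return the 18 per group that the section sets as its target. The comparison of 17.6 with 18 uses only the article's own figures and its rule that drop-outs leave the analysis.

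The cost in power is about one percentage point, and that figure rests on 18 giving exactly 80%. Without a defined effect-size metric, the article can neither confirm nor exclude true power below 80%, so the point should not be read as showing an underpowered trial. The origin of the 18 is a separate and larger question, which correcting the drop-out allowance does not settle. Severity: minor.

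**What to change.** Keep N = 66 and correct the sentence under Sample size calculation. It should say that 22 per group allows for 4 losses per group, about 18% drop-out, while still leaving 18, and that about 17 to 18 per group are expected if the loss reaches 20%. This costs one sentence and a slightly less favourable statement; recruitment, allocation and analysis are unchanged.

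If the sponsor prefers to keep the 20% allowance as stated, the matching figure is 23 per group, 69 in total with equal groups. That means three more participants and three more allocation envelopes, for a gain of about one point of nominal power. The article reports recruitment as still ongoing, so this is possible, but the size of the shortfall does not require it.
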